## Abstract

**Background:**

The changes in China’s family planning policy in recent years have led to changes in the age structure of pregnant women, and the prevalence of postpartum depression (PPD) is also on the rise. Cognitive Behaviour Training (CBT) as an effective intervention is widely used for postpartum depression. However, the shortage and health disparities of mental health resources, the stigma of postpartum depression in postpartum women and the need for postpartum recovery and child care prevent postpartum women from seeking traditional face-to-face CBT. Therefore, the purpose of this proposed study is to examine the effect of mobile phone applications (App) based CBT on postpartum depression, anxiety, pressure and parenting sense of competence.

**Methods:**

A double blind, randomized controlled trial will be used in this study to examine the effectiveness of App-based CBT in reducing the prevalence of postpartum depression compared with usual postpartum care in China. A total of 120 participants will be recruited in this study. The intervention consists of a weekly theme module app for continuous six weeks, each module including learning content and assignments. The control group received usual postpartum care content through the App. Outcome measures include postpartum depression, anxiety, pressure and parenting sense of competence at 0-, 3- and 6-month after the intervention.

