### Participants

This study will be conducted in Changsha city, which has five administrative district. We will randomly select one health center from all the community health centers in each district. Participants will be recruited from five community health centers we selected. Inclusion criteria:has Established maternal health care record in community health centers;0 days to 6 weeks after delivery;Score of 9–12 on the Edinburgh Postnatal Depression Scale (EPDS);Access to smart phone and able to independently use App;Informed consent and voluntary participation.

Exclusion criteria:Severe mental disorders (current or in the past);History of brain injury, intellectual disability or cognitive disorder; andUndergoing psychotherapy or any other psychological intervention.Patients diagnosed with postpartum depression or other severe mental illness during the study.

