### Measures

Measurements will be obtained at baseline (t_o_), immediately after the last intervention (t_1_), 3 months following the intervention (t_2_) and 6 months following the intervention (t_3_). The baseline data is collected when participants are enrolled, and after that, the data collection process will be implanted in the evaluation module of the mobile App. The primary outcome will be depression status. The secondary outcomes will be negative emotion symptoms including depression, anxiety and stress, parenting confidence. These will be measured as follows:*Demographic and Socioeconomic factors:* the information about Risk factors will be collected by demographic questioner including pregnancy and birth history, obstetric complications, delivery mode, baby gender, baby weight, baby health status, feeding pattern, satisfaction with family care, major life events. The socioeconomic factors include maternal age, marital status, history of depression, family history of mental disorder, occupation, medical insurance, education level, family income, and religious belief.*Depression status:* We will use the Edinburgh Postnatal Depression Scale (EPDS) Chinese version to assess participant’s depressive status, as this scale is an effective self-screening tool for PPD. The EPDS to be used in this study was translated by Lee [35] the sensitivity was 82%, the specificity was 86%, the positive predictive value was 44%, and the negative predictive value was 97%. The scale includes 10 items. The recommended threshold is < 9: no depression; 9 is regarded as a probable case; and 13 or more as suspected depression.*Negative emotion symptoms:* We will assess negative emotion symptoms using the Depression, Anxiety and Stress Scale (DASS-21), which is a self-report measure of anxiety, depression and stress levels used in diverse settings developed by Lovibond [36]. The Chinese version of DASS-21 was developed by Taouk ^[40]^ in 2001. This version was tested in Australian-Chinese speaking samples and Hong Kong-Chinese speaking samples, and indicated that the items had been adequately and appropriately translated and adapted. Wen Yi et al. [37] tested DASS-21 in 730 Chinese adults (over 18 years old), the result showed that the Cronbach’s α was 0.912 and the test-retest Pearson correlation coefficient was 0.751.*Parenting competence:* Parenting competence will be assessed using the Chinese version of Parenting Sense of Competence Scale (C-PSOC). The initial Parenting Sense of Competence Scale was an English version developed by Gibaud-Wallston [38]. In 2014 Chinese researcher, Yang Xiao translated it into Chinese and applied to Chinese population. C-PSOC includes efficacy and satisfaction factors and has 17 items. The Cronbach’s coefficient, efficacy factor and satisfaction factor of C-PSOC were 0.82, 0.80 and 0.85 respectively [39].

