### Sample size

A power analysis was performed for linear regression using University Dusseldorf G*Power 3.1 to determine the sample size necessary for analysis. The main objective of this study is to assess the effectiveness of App-based CBT on PPD high-risk mothers. According to previous studies, an effect size of 0.43 will be adopted [40]. The power analysis based on the conventional significant alpha level of 0.05 and a power of 0.90 using a two-tailed test. We calculate that the sample size required is 48 in each group. Considering a 20% dropout rate, the recruited sample size required in each group is 60.

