## Discussion

In China, although existing maternal health care regulations clearly propose to provide mental health services during pregnancy and postpartum, most of those services are carried out in hospitals, which reduce their accessibility to some women especially in the postpartum period. There are some health programmes for pregnant women organized by the hospital or community which provide information about mental health, but that is only for pregnant women with no follow-up available. With the advancement of graded diagnosis and treatment of public health, postnatal home visits have become a routine service for community work [41]. Usually, during the first 6 weeks following childbirth community medical professionals will conduct regular visits but the mental health status is not included in the visit. Therefore, developing a systematic, continuous, and accessible psychological intervention is essential. To the best of our knowledge, this proposed study will be the first intervention study to apply CBT to women with PPD through mobile health technology.

The highlight of this study was the application of App-based CBT to postpartum women. Ensuring the effectiveness of intervention is the key to this study. Firstly, the provider of intervention must be professionally trained and supervised [42, 43]. In our research, the intervention program was developed with the participation of psychologists to ensure the professionalism of the CBT program. Secondly, we conducted a survey on the form, frequency, and duration of intervention before the intervention was made to ensure the feasibility of intervention. Within those, the effectiveness and operability of interventions will be guaranteed.

In recent years, the high prevalence of postpartum depression in China and the shortage of mental health service resources make it extremely urgent to effectively intervene postpartum depression. With the development of mobile health technology, this study provides a convenient and effective intervention measure for postpartum depression women. If our intervention program proves to be effective in reducing the prevalence of postpartum depression, this will not only provide convenient and effective intervention measures for postpartum depression and effectively saved mental health service resources, but will also provide evidence-based evidence for interventions based on mobile health technologies.

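### The claim of lower PPD prevalence, and of an intervention for women with PPD, does not match entry at EPDS 9–12 or a sample size based on linear regression

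*Protocol article*

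**What the plan says.** All references are to the protocol article.

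- **Objective (Abstract, Methods):** the trial is "to examine the effectiveness of App-based CBT in reducing the prevalence of postpartum depression compared with usual postpartum care in China".
- **Planned conclusion (Discussion):** it is conditioned on the same claim, "If our intervention program proves to be effective in reducing the prevalence of postpartum depression". The Discussion also says "this proposed study will be the first intervention study to apply CBT to women with PPD through mobile health technology".
- **Entry (Participants):** "Score of 9–12 on the Edinburgh Postnatal Depression Scale (EPDS", within six weeks of delivery. The exclusion list ends with "Patients diagnosed with postpartum depression or other severe mental illness during the study".
- **Outcome (Measures):** "The primary outcome will be depression status", assessed with the EPDS. The instrument is described thus: "The recommended threshold is < 9: no depression; 9 is regarded as a probable case; and 13 or more as suspected depression". The article calls the EPDS a self-screening tool.
- **Sample size:** "A power analysis was performed for linear regression", with an effect size of 0.43, two-tailed alpha 0.05 and power 0.90. The result is 48 per group, raised to 60 for 20% dropout. The same section describes the participants as mothers at high risk of PPD.
- **Analysis:** between-group contrasts at baseline and the three later assessments, with ITT named as the principle for missing data.

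**The concern.** The claim, the enrolled women and the sample size describe three different things. The claim is about how common PPD is and about women who have it. The women enrolled lie between the two EPDS thresholds that the article names. The sample size is for a regression effect and involves no proportion.

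The same follow-up data could therefore be reported as a score difference, as fewer women reaching 13, or as more women falling below 9. These can give different answers, and the objective points to a fourth quantity, PPD prevalence. If the plan is followed as written, a favourable result would be announced as a reduction in PPD prevalence and as a treatment for PPD, which goes beyond what the design can show. The exclusion tied to diagnosis during the study adds to this. If it is applied after randomisation, it removes the very women a case-based outcome has to count.

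**Working it through.** **1. Baseline status at the article's own thresholds.** Every entrant scores 9, 10, 11 or 12.

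| Case definition | Baseline proportion | What a later contrast measures |
|---|---|---|
| EPDS ≥ 13 | 0% in both arms | progression |
| EPDS ≥ 9 | 100% in both arms | remission (falling below 9) |

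A cut-off of 10, 11 or 12 would give an intermediate baseline value, but the article names none of these.

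**2. The stated sample size.** The dropout step reproduces: 48 / (1 − 0.20) = 60 per group, 120 in total. The 48 does not reproduce if 0.43 is a standardised mean difference:

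n per group = 2 × (1.960 + 1.282)² / 0.43² = 2 × 10.51 / 0.1849 ≈ 114

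The exact t calculation gives 115, and 48 per group would then have about 55% power. Other readings of 0.43 land near 48 per group only with unstated inputs. For example, f = 0.43 with five tested predictors gives a total of 95. A bivariate slope of 0.43 gives 49 in total, not per group. The article does not state the metric, so the 48 is unverified. None of these readings is a calculation for a difference in proportions.

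**3. What 48 per group would give if a proportion were primary.** The article gives no control rate for women entering at EPDS 9–12, so the rates are assumptions. Its 25% is a general PPD prevalence in China and serves here only as one point in a range. For a two-sided 0.05 test with pooled null variance, where p̄ is the mean of p₁ and p₂:

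power = Φ{ [ |p₁ − p₂| − 1.96 √(2 p̄(1 − p̄)/n) ] / √( [p₁(1 − p₁) + p₂(1 − p₂)]/n ) }

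For 25% versus 12.5% with n = 48, p̄ = 0.1875, the null standard error is √(0.3047/48) = 0.0797 and the alternative is √(0.2969/48) = 0.0786. Power = Φ[(0.125 − 0.1562)/0.0786] = Φ(−0.40) ≈ 0.35.

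| Control vs intervention (assumed) | Power, 48 per group | Power, 60 per group (no dropout) | n per group for 90% |
|---|---|---|---|
| 25% vs 12.5% | 35% | 42% | 203 |
| 40% vs 20% | 57% | 67% | 109 |
| 50% vs 25% | 72% | 82% | 77 |

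With 48 per group, 90% power needs a fall from 25% to about 2.6%, from 40% to about 12%, or from 50% to about 19%.

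**4. The exclusion and the analysis principle.** Risk management sends women with EPDS above 12 to a psychologist, and such a referral can lead to a diagnosis. The exclusion list then names patients diagnosed during the study, while Analysis invokes ITT. If the exclusion applies after randomisation, the two conflict for exactly the women who progress.

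**The case against.** The strongest reply is that the objective is comparative. It sets the intervention against usual care, and Analysis plans contrasts between arms. A baseline proportion of 0% or 100% is the same in both arms and does not bias the follow-up comparison. At the threshold of 13, a lower proportion than in the control arm is what successful prevention looks like. At 9, the proportion can fall from 100%. All of this stands. A reader might infer from the fixed baseline that the comparison is invalid, or that the data could support no statement about cases at all. The documents support neither reading. What the contrast cannot do is speak for postpartum women in general or for women with PPD.

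Second, the article already leans towards prevention in places. Sample size speaks of high-risk mothers, Blinding says participants will be told the programme is meant to protect against PPD, and the purpose statements in the abstract and Background do not mention prevalence. That is fair. It means the correction falls mainly on the abstract's Methods and the Discussion.

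Third, the thresholds are introduced as a description of the instrument, and the choice between score and cut-off may be settled in a document not shown. This also stands, so the point does not rest on a missing definition. It rests on an objective, a population and a sample-size basis that disagree within the article.

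Fourth, no two-proportion test is planned. The power table is therefore conditional. It does not show that the trial as planned has 35% power.

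Last, the reported positive predictive value of 44% is not relied on here, because its cut-off and the prevalence in the validation sample are not given.

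**Conclusion.** The mismatch is real and should be corrected. The article concludes on PPD prevalence and on women with PPD. It enrols women at EPDS 9–12, lists patients diagnosed during the study under exclusion, and sizes the trial without an event rate. A case-based result would show progression or remission on a screening tool in a sub-threshold group.

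The fit between claim, population and sample-size basis can be read directly from the text and needs no assumption. The size of the power shortfall does rest on assumptions. Over the control risks tried (25% to 50%), a halving would have about 35% to 72% power with 48 per group, and only if a proportion were made primary. The randomised comparison itself is not in doubt on this ground.

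**What to change.** 1. Name the EPDS total score, as a continuous variable, as the primary outcome. This is consistent with the linear-regression basis in Sample size.
2. List the proportion with EPDS ≥ 13 (progression) and the proportion with EPDS < 9 (remission) as secondary outcomes under those labels.
3. State that women diagnosed during the study are counted in the outcome analysis, and reconcile the exclusion entry in Participants with the ITT principle in Analysis.
4. Reword the objective in the abstract and the conclusions in the Discussion to refer to depressive symptoms, or progression, in women with EPDS 9–12. Remove the references to PPD prevalence and to women with PPD.
5. Re-derive the 48 per group separately, stating the metric of 0.43 and the model. Making the score primary does not confirm that number: if 0.43 is a standardised mean difference, about 114 per group are needed.

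Items 1, 2 and 4 change wording only and need no new measurements. Item 3 means keeping these women's follow-up data in the analysis. Item 5 may change the sample size. The cost is a narrower claim.

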**Discussion:**

If our intervention is effective, it will provide a time-friendly and unrestricted intervention for the psychological care of perinatal women, which can effectively solve the shortage and unevenness of mental health resources.

**Trial registration:**

Chinese Clinical Trial Registry, ChiCTR1900020735. Registered 15 January 2019.

## Background

Mental health has become a global issue for public health. The global burden of disease 2016 (GBD 2016) confirmed that the major cause of non-fatal burden was mental disorders and substance use disorders, led by depressive disorders [1, 2]. Postpartum depression (PPD) as a disabling but treatable mental disease is one of the most common mental health issues faced by post-natal women. The Diagnostic and Statistical Manual of Mental Disorders, Fifth Edition (DSM-5) defines PPD as a major depressive episode that occurs during pregnancy or within 4 weeks of delivery [3]. This is because the effects of biological factors on women’s emotions are significantly reduced impacted within 4 weeks after birth. However, the pressures of parenthood faced by some postpartum women are difficult to alleviate, and depression during this period continues to have negative consequences, which require medical treatment [4, 5]. Therefore, in the current study focusing on PPD, the postpartum period is defined as one year after birth [6].

According to a report conducted by World Health Organization (WHO) [7], approximately 10% of pregnant women and 13% of women who have just given birth worldwide suffer from mental disorders, mainly depression. A recent meta-analysis of studies from 56 countries showed that the global prevalence of PPD is about 17.7% [8]. The national differences in the prevalence of PPD is mainly reflected in higher prevalence among women in lower-income and middle-income countries [9–11]. Studies in China in recent years have shown that the prevalence of PPD is approximately 25% [12, 13], which is higher than the global average. That may be partly due to the special condition of fertility policy in China. As an effective approach to decelerate the growth of population, the one-child policy has been implemented in China since the 1980s. Now the first generation of ‘only children’ following the implementation of that policy has reached reproductive age. Some research shows that women from one-child families are more likely to have PPD [14, 15]. Moreover, with the recent change of family planning policy in China, many women have more than one child now. This has resulted in the changing age structure of pregnancy women, which is a clear factor for the increased proportion of advanced maternal age (AMA) [16]. This change may consequently increase the prevalence of PPD by increasing pregnancy complications as well other adverse pregnancy outcomes [17, 18].

As one of the most common mental health disorders during the postnatal period, the negative effects of PPD involve many aspects of daily life. These include lower quality of life for women [19], physical and psychological developmental disorders in children [20], and lower marital satisfaction [21]. Psychological interventions including health education, interpersonal psychotherapy (IPT), cognitive behaviour training (CBT) and problem focused therapy have been the main interventions for PPD due to concerns about the adverse effects of pharmacology therapy on breast feeding infants [22]. Among these psychological therapies, CBT is considered to be the most widely used. The effectiveness of CBT in mild to moderate depression has been demonstrated in many studies [23, 24]. Multiple guidelines and expert consensus also recommend CBT as an effective psychological intervention for PPD [25, 26]. Nevertheless, there are still many barriers to the successful implementation of face to face CBT in the postpartum population. First, the shortage and health disparities of mental health resources, for example lack of mental health care workers, hinder the accessibility of mental health services [27]. Second, the stigma of PPD blocks seeking “face-to-face” mental health services, which are particularly prominent in lower-income and middle-income countries [28–30]. Lastly, the challenge of finding time for mothers to participate in the psychological intervention while trying to take care of their babies is also another barrier [27].

With the development of internet technology and mobile health in recent years, Computerised Cognitive Behavioural Therapy (CCBT) as well as health promotion mobile phone applications (App) have been used in many countries for the treatment of depression [31], anxiety [32] and insomnia [33]. In recent years, the continuous development of mobile communication networks and the wide application of smartphones have also provided new ways to realize psychological interventions based on mobile health technologies. It is reported that [34], as of June 2016, the number of mobile internet users in China reached 656 million, and the internet access equipment was further concentrated to the mobile terminal, which laid the foundation for the development of health services based on mobile health technology. CCBT and App-based CBT are easily accepted by postpartum women because of their flexibility in participation time and confidentiality of participant information. And for the providers of mental health services, CCBT and App-based CBT provide a good solution of the shortage of the mental health services resources. However, there is no currently CCBT or App-based CBT for women with PPD. Therefore, the purpose of this proposed study is to examine the effect of App-based CBT on psychosocial outcomes (including postpartum depression, anxiety, pressure and parenting sense of competence).

Based on this, we hypothesize that the App-based CBT will enable mental health services to be delivered to perinatal women in a more convenient, flexible and personalized way so that it can avoid the disadvantages of traditional CBT in terms of accessibility for perinatal women.

## Methods/design

### Design

A double blind, randomized controlled trial (RCT) will be used in this study. All participants who met the inclusion criteria were randomly assigned to the intervention group or control group for a six-week intervention program.

### Participants

This study will be conducted in Changsha city, which has five administrative district. We will randomly select one health center from all the community health centers in each district. Participants will be recruited from five community health centers we selected. Inclusion criteria:has Established maternal health care record in community health centers;0 days to 6 weeks after delivery;Score of 9–12 on the Edinburgh Postnatal Depression Scale (EPDS);Access to smart phone and able to independently use App;Informed consent and voluntary participation.

Exclusion criteria:Severe mental disorders (current or in the past);History of brain injury, intellectual disability or cognitive disorder; andUndergoing psychotherapy or any other psychological intervention.Patients diagnosed with postpartum depression or other severe mental illness during the study.

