### Analysis

This study used double data entry. Data entrants, analysts, and data custodians do not participate in the intervention process. Analyses will be performed using SPSS (version 20.0; SPSS Inc., Chicago, Ill). All tests of significance will be determined at an alpha level of 0.05. The principle of ITT will be used to handle missing data. We plan to analyse contrasts between intervention and control groups at baseline, post intervention, 3 months and 6-months follow-up.

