### Risk management

In our study, participants have to complete EPDS at baseline, immediately after the intervention, three months after the intervention, and six months after the intervention. We will refer the participants to psychologist immediately after we found participants who had EPDS scores greater than 12. Each participant is entitled to withdraw from the study during the intervention, when they decided to withdraw from the study, our research team will assess their situation to see if they needed to be transferred to psychologist.

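### A diagnosis of postpartum depression made during the study is an exclusion criterion, so women can be removed after randomisation for an event tied to the primary outcome, in conflict with ITT

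*Protocol article*

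**What the plan says.** All of this is in the protocol article.

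- **Participants.** Women enter with "Score of 9–12 on the Edinburgh Postnatal Depression Scale (EPDS"). The exclusion list contains "Severe mental disorders (current or in the past") and, as a separate item, "Patients diagnosed with postpartum depression or other severe mental illness during the study".
- **Randomization.** Allocation is automatic once the baseline survey has been completed.
- **Measures.** "The primary outcome will be depression status", assessed with the EPDS at baseline (t0), after the last module (t1), and 3 and 6 months later (t2, t3). The scale's upper category is "13 or more as suspected depression".
- **Risk management.** "We will refer the participants to psychologist immediately after we found participants who had EPDS scores greater than 12". The EPDS is to be completed at all four time points.
- **Analysis.** "The principle of ITT will be used to handle missing data". Between-group contrasts are planned at every time point.

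The abstract and the Discussion describe the aim as lowering the prevalence of postpartum depression.

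**The concern.** An exclusion criterion normally describes a woman's state before she is randomised. This one describes something that happens to her afterwards, and that event is the condition the trial is meant to reduce. If a woman leaves the study when she is diagnosed, whether she is observed at later visits depends on how she is doing. How she is doing may in turn depend on her arm.

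The groups compared at t2 and t3 would then no longer be the groups that were randomised. ITT offered as a way to handle missing data does not repair this: the missing values would be produced by the plan's own rule, and would be missing because of poor outcome. Scores that are never collected cannot be recovered by any later analysis.

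The complaint is not about detail that belongs in an analysis plan. A stated eligibility rule conflicts with a stated analysis principle, and an analysis plan that followed the protocol would inherit the conflict.

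**Working it through.** **Step 1: does the rule act after randomisation?** Severe disorder present at entry or earlier is already excluded by its own item. What the disputed item adds is diagnoses made later. Randomisation follows at once on completion of the baseline survey, so practically all of the study period, and with it practically every diagnosis the item covers, comes after allocation.

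**Step 2: is it tied to the primary outcome?** All women start at EPDS 9–12, just under the 13 threshold. The score that puts a woman in the worst outcome category (13 or more) is the score that sends her to a psychologist (above 12). These are the same whole-number scores. A psychologist's assessment may lead to the diagnosis that excludes her. Because nobody enters above 12, this route first opens at t1, and no survey follows t3.

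**Step 3: does any text retain these women?** Risk management speaks of referral and of voluntary withdrawal. Analysis speaks of ITT for missing data. Neither says that a diagnosed woman stays in follow-up or in the analysis.

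**Step 4: how large could the effect be?** No figure in the plan decides this, so what follows is an illustration.

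*Inputs.* From the protocol: effect size 0.43 (its metric is not stated; taken here as a standardised mean difference), cut-off above 12, 60 recruited per group, 20% dropout. Assumed: control follow-up EPDS mean 9–10, SD 4–5, correlation between visits 0.3–0.7, scores rounded and held within 0–30, the same arm means at t1, t2 and t3.

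*Share above 12 at a visit.* P(score ≥ 13) = P(Z > (12.5 − mean)/SD), with App mean = control mean − 0.43 × SD.

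| Control mean, SD | Control | App |
|---|---|---|
| 9, 4 | Z > 3.5/4 = 0.875: 19% | mean 7.28; Z > 5.22/4 = 1.305: 10% |
| 10, 5 | Z > 2.5/5 = 0.50: 31% | mean 7.85; Z > 4.65/5 = 0.93: 18% |

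*Removed before t2 if 44% of these are diagnosed and excluded.* Controls: 0.44 × 19.1% = 8.4% to 0.44 × 30.9% = 13.6%, or about 5 to 8 of 60. App: 0.44 × 9.6% = 4.2% to 0.44 × 17.6% = 7.7%, or about 3 to 5 of 60. The whole dropout allowance is 0.20 × 60 = 12 per group.

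*Effect on the mean difference.* Three correlated scores per woman were simulated. A woman scoring above 12 at one visit was removed from all later visits with probability 0.44 or 1. The score that triggered referral was kept. Ratio = (control mean − App mean among women still present) / (the same difference among all randomised women).

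| Removed among those above 12 | t1 | t2 | t3 |
|---|---|---|---|
| 44% | 100% | about 90–96% | about 81–93% |
| All | 100% | about 67–90% | about 57–82% |

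The loss grows with the correlation between visits and from t2 to t3. Even when all are removed, the proportion scoring 13 or more among women still present does not reach zero.

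**Step 5: direction.** In this model the App works and the chance of diagnosis given a high score is the same in both arms, so more controls are lost and the effect is diluted. The intervention's first module, however, teaches postpartum depression symptoms and self-evaluation (Table 1), and the control modules do not. If that raises diagnosis in the App arm, the bias can run the other way.

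**The case against.** The strongest reply is that removal from the analysis is inferred, not stated. The item could be a badly placed rule for stopping the App; Risk management mentions only referral; and Analysis names ITT. This stands in part. The article does not say whether exclusion means leaving treatment, follow-up or analysis. But the item sits among the eligibility exclusions, where the natural reading is removal from the study, and no text rescues the other reading. The passages need reconciling whichever was meant.

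A reader might go further and infer that the rule deletes the primary outcome's failures, so that no woman scoring 13 or more is left in either arm and the mean difference falls to 52–65% of the truth (43–74% under wider assumptions). The documents do not support that, for two reasons:

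- Those figures require deleting the very score that led to referral. That score is recorded before any referral or diagnosis, and no text says it is discarded.
- The rule turns on a diagnosis and the outcome on a screening score. Diagnosed women are only some of those scoring 13 or more.

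The 44% is also open to challenge. Measures reports that "the positive predictive value was 44" per cent, but does not tie it to a cut-off, and this cohort is pre-selected at 9–12. Here it serves only as an assumed rate of diagnosis and removal, with full removal as the upper bound.

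**Conclusion.** The conflict is real and rests on the text alone. An exclusion criterion acts after randomisation, on an event linked to the primary outcome, alongside a commitment to ITT and with no statement that the women concerned are retained.

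The size depends on the assumptions listed. With removal only from visits after a score above 12, there is no effect at t1. With partial removal the loss is modest (about 4–10% of the true difference at t2 and 7–19% at t3). With full removal it is substantial (about 10–33% and 18–43%). It would be larger if data already collected were also deleted. A diagnosis reached outside the study's referral route before t1 would affect t1 as well; the illustration leaves that out.

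A reader might take dilution of the effect as certain. It is not: it holds when the App is beneficial and diagnosis given score is equal in the two arms, and neither is known in advance.

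**What to change.** Reconcile Participants, Risk management and Analysis by stating that:

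1. for the purposes of data collection and analysis, exclusion criteria apply only to a woman's status before randomisation;
2. every randomised woman stays, with her consent, in EPDS follow-up through the App and in the primary analysis in her allocated group, whatever diagnosis or referral follows;
3. a diagnosis made during the study is recorded, with its date, as an outcome or intercurrent event.

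Whether the intervention continues after a diagnosis, and all clinical care, remain for the investigators; nothing here changes the referral. The cost is a short change of wording and continued EPDS collection from women who are already enrolled, using the survey module already built into the App.
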